## Abstract

This manuscript describes the rationale and protocol of a school-based randomized controlled trial called “Cycling and Walk to School” (PACO, by its Spanish acronym) that aims to promote cycling to and from school and physical activity (PA) in adolescents. This study will examine the effects of this intervention in cycling and active commuting to and from school (ACS), PA and several ACS-related factors based on self-determination theory (SDT) and a social-ecological model (SEM). A total of 360 adolescents attending six high schools (three experimental and three control) from three Spanish cities will participate in this randomized controlled trial. The intervention (four cycling sessions; 1–2 h per session, one session per week) will be conducted by the research staff; the control group will continue their usual activities. PA levels will be measured by accelerometers, whereas ACS and the other study variables will be self-reported using questionnaires at baseline and post-intervention. The primary outcomes will be: rates of cycling to school, ACS and PA levels. In addition, SDT-related variables and individual, interpersonal, community, and environment variables relevant to ACS will be based on SEM. The findings will provide a comprehensive understanding of the short-term effects of this school-based intervention on cycling to school behaviour, ACS and PA levels in Spanish adolescents.

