#### 2.3.3. Sample Size Calculations

A minimum sample size of 300 participants will be needed to detect an odds ratio of 1.5 in the primary outcome (i.e., PA), assuming an alpha error of 0.05 and 80% of statistical power [51]. Therefore, 50 participants regardless of gender per school (6 schools) are needed. To account for the potential loss to follow-up of up to 50% participants regardless of gender (based on investigators’ previous experience due to the use of wearable devices), a total of 360 adolescents will be recruited (i.e., 120 participants per city). The groups randomization will be done at a 1:1 ratio at city level (i.e., from each city, 60 participants will be randomized to intervention and 60 to control groups).

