### 4.2. Outcome Measures

The primary outcomes are adolescent´s behaviours (i.e., cycling to school, ACS–walking and cycling, and PA). Other variables include a range of individual, interpersonal, and environmental factors that are related to ACS (see Table 1), and they will be potential mediators or covariates in the statistical analysis. All the questionnaires self-reported by students will be compiled in a global Student questionnaire; and all the questionnaires self-reported by families will be compiled in a global Family questionnaire.

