PA will be measured objectively with a triaxial accelerometer (Actigraph wGT3X-BT, Pensacola, FL, USA) for 7 consecutive days, during waking time. Adolescents will be instructed to use an accelerometer attached to the waist on the right side of the body. Additionally, they will be instructed in the care of the device and it will be removed during water activities and sleeping time during night. Students will also complete an activity diary to record when the accelerometer is removed, the time when they wake up and go to sleep, as well as, the time when they go out from home to school. The Actilife software (Actigraph, v.6, Pensacola, FL, USA) will be used both for the initial configuration before the evaluations and for the data dump registered during the evaluation week. Accelerometers should be programmed with a frequency of 90 Hz and an epoch length of 15 s according to the recommendations for the sample of this study (adolescents) [70]. The final variables to analyse will be the daily minutes of light, moderate, vigorous, moderate to vigorous, and total PA.

In addition, we will also extract accelerometer data from specific times of the day for each participant, calculating the PA during commuting from home to school, commuting from school to home, in-school and out-of-school hours. Participants will carry a GPS (model Q STARZ BT-Q1000XT -Q STARZ International Co., Ltd. Taipei, Taiwan) on the left side of the body on the same belt of their accelerometer during the last two consecutive week days carrying the accelerometer.

Moreover, the PA will be self-reported through the questionnaire Youth Activity Profile, which provides a simple, low-cost, and educationally sound method that have already been calibrated and validated to accurately estimate children’s MVPA and sedentary behaviour at the group level [71,72]. A Spanish version of the Youth Activity Profile questionnaire was elaborated using a back-translation process and it has been shown to be a feasible and reliable questionnaire in Spanish adolescents [63]. The Youth Activity Profile questionnaire includes a total of 19 items, including 4 general items and 15 specific items divided into three sections: (1) activity at school, (2) activity out of school, and (3) sedentary habits. The final variables to analyse will be an average score ranging from 1 to 5 (lowest to highest) about the PA at school and PA out-of-school.

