## 6. Data Analysis

Descriptive characteristics of the sample will be reported as means and standard deviations for continuous variables, and frequencies and percentages for categorical variables. Analysis of variance and Chi-square tests will be conducted to determine differences in all variables between study group (i.e., control or intervention) at baseline.

Firstly, the appropriateness of the randomization process will be analysed by exploring outlier values and the normal distribution of the variables using the Kolgomorov–Smirnov test and graphical procedures (normal distribution plots). After inspecting outliers and extreme values, these will be winsorized using the 1st percentile and 99th percentile of the distribution of variables.

Secondly, analysis of covariance (ANCOVA) will be used to analyse the main effects of the study group (fixed factor) on cycling to school, ACS, PA levels, SDT-related variables in ACS, and individual, interpersonal, and environment variables related to ACS from the SEM (dependent variables). The effect size between groups will be calculated according to Lipsey and Wilson (2001), with the following formula: r = [t^2^/(t^2^ + gl)], where t = value of the Student t statistic and gl = degrees of freedom. Additionally, to examine change between baseline and post-intervention, regression models will be used, including the study group in the model as fixed factor and the mean difference (post-intervention minus baseline) of outcome variables as dependent variable.

Finally, to analyse the influence of covariates in the association of the intervention and the main outcome (i.e., cycling to school, ACS, and PA levels), mediation analyses will be performed using the PROCESS macro for SPSS (SPSS Inc., Chicago, IL, USA). For these analyses, the intervention will be included as independent variable and main outcomes as dependent (i.e., cycling to school, ACS and PA levels). Mediators that will be analysed are cycling knowledge, cycling skills, basic psychological needs satisfaction in ACS, motivation for ACS, barriers to ACS from adolescents and parents, and peer social support for ACS.

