The following covariables will be included in the regression models: children´s age and gender, date of birth, school grade and name, class, bicycle ownership, parent´s age and gender, weight, height, waist circumference, body mass index, family income, parental educational level, student enrolment, school socioeconomic status, school engagement, population density, city income, distance home-school, cycling lane length, bicycle racks and weather.

Considering that our main aim is to assess real-world effectiveness of the intervention, we will conduct a primary analysis based on an intention-to-treat principle (in which we will analyse participants according to the groups originally assigned). Then, we will conduct a sensitivity analysis per protocol (in which we will exclude participants who did not complete the intervention and/or did not reach a minimum of 75% of attendance).

Analyses will be conducted using the Statistical Package for Social Sciences (SPSS, v. 25.0, IBM SPSS Statistics, IBM Corporation), and the level of significance will be set at *p* < 0.05.

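### The power section names one primary outcome where the Abstract and Section 4.2 name three, and the change-score regression added to the ANCOVA omits the baseline value of the outcome

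*Protocol article*

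**What the plan says.** **Primary outcome.** The Abstract states: "The primary outcomes will be: rates of cycling to school, ACS and PA levels". Section 4.2 repeats the three behaviours: "i.e., cycling to school, ACS–walking and cycling, and PA". Section 2.3.3 is written for one outcome. It says "A minimum sample size of 300 participants will be needed" and that this number serves "to detect an odds ratio of 1.5 in the primary outcome (i.e., PA", with alpha 0.05 and 80% power. Section 4.2.1 then gives the accelerometer variables for PA: "The final variables to analyse will be the daily minutes of light, moderate, vigorous, moderate to vigorous, and total PA".

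**Model.** Section 6 uses ANCOVA for the main effect of study group on the three behaviours and on the theory-based variables. It does not name the ANCOVA covariate. It then adds regression models, meant to look at change, with study group as fixed factor and "the mean difference (post-intervention minus baseline) of outcome variables as dependent variable". The covariates of the regression models follow as an explicit list of 24 entries (counting weather as one), from age and gender to bicycle racks. The baseline value of the outcome is not among them. For all analyses "the level of significance will be set at" 0.05.

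**The concern.** There are two separate defects in the stated text.

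First, the sections disagree on what is primary. The sample size and its 80% power belong to one outcome, while the aims and the outcome section carry three. A reader cannot tell whether the stated power is meant to cover cycling to school and ACS, or whether those two were never part of the design calculation. No later analysis plan can agree with both statements.

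Second, the same group effect is estimated in two ways, and the second is the less efficient one as written. The outcome at baseline is usually the strongest predictor of the outcome at follow-up. A list that goes down to waist circumference and bicycle racks but omits it gives away precision that costs nothing to keep. The two estimates can also fall on opposite sides of 0.05 for the same variable.

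**Working it through.** **1. The plan's own figure.** Section 2.3.3 states 300 for an odds ratio of 1.5, alpha 0.05 and power 80%. It gives no control rate, so I tried rates from 0.003 to 0.50 with the pooled two-proportion formula. The smallest total occurs at a control rate of 0.45:
- intervention odds = 1.5 × 0.45/0.55 = 1.227, so the rate is 1.227/2.227 = 0.551
- total = 768 two-sided, or 604 one-sided

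So 300 is not reproduced as a comparison of two groups, and the figure does not help to identify the outcome that was meant. An odds ratio describes a binary outcome, whereas the accelerometer variables in Section 4.2.1 are minutes. Both are side remarks; the conclusion below does not rest on them.

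**2. The outcome statements side by side.**

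| Place | Named as primary |
|---|---|
| Abstract | cycling to school, ACS, PA |
| Section 4.2 | cycling to school, ACS, PA |
| Section 2.3.3 | PA |

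This is a contradiction in the text, not an omission.

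**3. Precision of the change score.** Let r be the correlation between baseline and follow-up, with equal variance s² at both times and no other covariates.
- Change score: variance per person = 2s²(1 − r)
- Baseline-adjusted: variance per person = s²(1 − r²)
- Ratio = 2(1 − r)/(1 − r²) = 2/(1 + r)

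| r (assumed) | Ratio |
|---|---|
| 0.3 | 2/1.3 = 1.54 |
| 0.5 | 2/1.5 = 1.33 |
| 0.7 | 2/1.7 = 1.18 |
| 0.8 | 2/1.8 = 1.11 |

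**4. Can the two tests disagree?** Under no effect, the two test statistics have correlation √((1 + r)/2), which is 0.866 at r = 0.5 and 0.922 at r = 0.7. The bivariate normal distribution gives the chance that at least one rejects at two-sided 0.05 as 7.3% and 6.8%. Both reject with probability 0.10 minus that figure, so exactly one rejects with probability:
- r = 0.5: 7.34% − (10% − 7.34%) = 4.7%
- r = 0.7: 6.81% − (10% − 6.81%) = 3.6%

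This is for one variable, with clustering ignored.

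**5. What the baseline covariate does.** Write the ANCOVA as Y = a + b·group + c·X + error, where X is the baseline value. Subtracting X from both sides gives Y − X = a + b·group + (c − 1)·X + error. The coefficient b, its standard error and its p-value are unchanged. In one simulated data set (150 per arm):

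| Model | Group effect | p |
|---|---|---|
| ANCOVA with baseline | 0.239 | 0.044 |
| Change score with baseline | 0.239 | 0.044 |
| Change score without baseline | 0.219 | 0.087 |

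The example illustrates the identity; it is no forecast for this trial.

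**6. Cost of a multiplicity method, if three primaries are kept.** Holm's first step tests at 0.05/3 = 0.0167, with critical value 2.394. For an outcome designed at 80% power:
- power = Φ(1.960 + 0.842 − 2.394) = Φ(0.408) = 66%
- sample-size factor to restore 80% = ((2.394 + 0.842)/(1.960 + 0.842))² = 1.33, so a nominal 300 becomes about 400

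**The case against.** The article is condensed and an analysis plan may exist. Such a plan could name the decisive variable within each behaviour and a rule for multiple tests. That stands, so the silence on these matters is not part of this point.

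The wording in Section 6 also puts ANCOVA first, for the main effects, and introduces the regression as an addition with its own purpose. A reader might infer two rival primary tests of equal rank. The text does not say so, and a supporting role is the more natural reading, although no order is written down.

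Two stronger readings are tempting. One is to compute a familywise error over all listed commuting and PA variables as if they were independent. They overlap by construction: moderate-to-vigorous PA contains moderate and vigorous PA, and ACS contains cycling. The unseen plan may also control the error. The other is to call the change score biased by chance baseline imbalance between the arms. With six schools such an imbalance may be largely a school-level matter, and an individual-level correlation does not describe how much of it persists. If school differences are stable over the month, the change score may carry less of it than an analysis using the within-school slope. The documents support neither inference.

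Finally, the variance ratios are for models without further covariates, whereas the plan lists 24. This limits the exact size. The listed covariates do not replace the baseline value of the outcome.

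**Conclusion.** The point holds in two parts. The contradiction over the primary outcome is certain and needs no assumption: three in the Abstract and Section 4.2, one in Section 2.3.3. The omission of the baseline value from the stated covariate list is also certain. Its cost is a change-score variance about 1.33 times the baseline-adjusted one at r = 0.5 and 1.18 times at r = 0.7, and a small chance that the two tests disagree. These sizes rest on assumed correlations and equal variances, and they ignore other covariates and clustering. That the ANCOVA itself adjusts for baseline is implied only by the name of the method.

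The finding is one of precision and of consistency in the text. It does not show that the plan inflates the overall type I error or that its estimates are biased.

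**What to change.** - In Section 6, state the main test in full: follow-up value on study group plus the baseline value of the same outcome.
- Add the baseline value of the outcome to the covariate list of the regression models. With the other covariates the same, the linear change-score model then gives the same group effect as the ANCOVA, and the two tests become one. If this is not wanted, report change descriptively, without a test.
- Reconcile Section 2.3.3 with the Abstract and Section 4.2. Either name one primary outcome throughout and call the other two secondary, or keep three and give a power statement that covers them. In both cases name the variable meant.
- Optional: if three are kept, a method such as Holm may be used. State its cost: about 66% instead of a nominal 80% power at the first step, or about 1.33 times the sample. That is not negligible in a trial whose Discussion lists low sample size as a limitation.

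The first two changes cost only wording, because Section 4.1 already plans the baseline assessments. The third is also wording if one outcome is chosen; keeping three requires a new power calculation.

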### 4.1. PACO Study Assessment Protocol

In the PACO study, assessments will be performed at baseline (before the 4-week intervention period) and immediately after the intervention period for both intervention and control groups (see Figure 5). A further detailed description has been published [58]. All measurements will be completed at participant’s school by trained research staff during 3 assessment sessions conducted over 9 days both at baseline and after the intervention period:Assessment session 1 (1 h): this session will include anthropometry assessment at an indoor sport facility. During this session, participants will receive their accelerometer and the activity diary as well as a family questionnaire for their parents to complete at home.Assessment session 2 (1 h): participants will receive their GPS unit and corresponding instructions.Assessment session 3 (1 h): during this classroom-based session, participants will return their accelerometer, the activity diary, the GPS unit, and the completed family questionnaire. During this session, participants will also complete a student questionnaire online or on paper. The questionnaires will be subsequently read using DataScan [59] to guarantee an objective process.

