In the search for balance, several pragmatic adaptations will be made to conduct the research in “real-world” scenarios (such as school) where decisions need to be made on how to best conduct the study with the limited amount of time and resources that researchers may have [82]. In the PACO study, these adaptations pertain to the study design, implementation, and evaluation. Firstly, the school teachers will be able to choose the participating class groups, within the same grade. The pilot study and several consultations with school teachers showed that teachers want to choose the participating class and this will increase their involvement in the intervention. Secondly, all high schools in the three participating cities will be included in the random selection processes and then, the chosen schools will be invited to participate. Time limitations do not allow to visit each school for this purpose, and emails to schools have been previously sent (in previous studies of the research group) and they have not been answered because of high workload. Consequently, we will include all the schools in the random process to guarantee that everyone has the same likelihood to be selected. Thirdly, the intervention includes 4 sessions during a 1-month period. Research staff will offer the option to teachers of spreading the 2 h lesson of the 2nd and 4th session in two 1 h sessions using the normal PE schedule. In Spain, the national educational system in secondary schools mandates 2 h per week of PE. Fourthly, regarding the organization of the academic year in 3 trimesters, the study will be implemented in full trimesters to avoid holiday times, including the assessments. Finally, the cycling skills will be assessed by the teacher using a checklist twice during the intervention, simulating real evaluation conditions. However, safety (e.g., to avoid risky activities where children perform skills that they have not learned yet) and time limitations (e.g., lack of more PE sessions to enlarge the intervention), will prevent the cycling skills assessment being carried out at baseline and follow-up, respectively. To summarize, doing research in schools is important to prevent unhealthy behaviours and related beliefs common in our society. Achieving a balance between the scientific requirements of randomized designs and the constraints imposed by real world circumstances is necessary to improve the quality of research conducted in educational settings [83]. It is also consistent with recent calls to achieve a balance between the established evidence-based pathway and a practice-based evidence pathway, and for a more nuanced approach to appraising the utility of diverse types of evidence [84].

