
The intended outcomes in the PACO study are to increase the number of participants using cycling or other active modes of commuting to school and PA levels. However, there is evidence about the difficulty of changing behaviours though school-based interventions. For example, the rigorously developed school-based Go Active intervention was no more effective than standard school practice at increasing adolescent PA [83]. Therefore, mediators must be measured to identify the pathways for achieving future behaviour changes. Actually, previous reviews of school-based interventions to promote ACS concluded about the lack of inclusion of mediators in the statistical analyses [22,25]. In the current study, an in-depth analysis of mediators is proposed based on SDT and SEM. The effects of the intervention in the mediators, as well as possible effects of the mediators on the main outcomes, will be analysed. The presence of an appropriate control group is crucial to assess the effects of the intervention. The findings from the PACO study will extend current knowledge about the effectiveness of a cycling school-based interventions to increase active modes of commuting and physical activity levels among secondary school students.

Strengths of the PACO study include the study design (i.e., randomised controlled trial), the inclusion of proposed mediators of the effects of the intervention, the use of theoretical frameworks (i.e., SDT and SEM) and the use of internal and external validity indicators of study design and assessment of implementation processes guided by the RE-AIM framework. The limitations include the low sample size, the short duration of the intervention, the lack of family involvement in the intervention, uncertainties surrounding the engagement and cooperation of school teachers, and the lack of assessment of cycling skills and the maturity at baseline and post-intervention.

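### The mediation plan and its covariate list name no baseline mediator or baseline outcome, so a pre-existing correlation can pass for a mediated effect

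*Protocol article*

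**What the plan says.** Section 6 (Data Analysis) describes the PROCESS models in a few lines. On exposure and outcome it says: "For these analyses, the intervention will be included as independent variable and main outcomes as dependent", the outcomes being cycling to school, active commuting and physical activity. On mediators: "Mediators that will be analysed are cycling knowledge, cycling skills, basic psychological needs satisfaction in ACS, motivation for ACS, barriers to ACS from adolescents"; parental barriers and peer social support complete the list. It does not say whether mediators and outcomes enter as post-intervention or change values, and it names no baseline term.

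The next paragraph begins "The following covariables will be included in the regression models" and lists demographic, anthropometric, socioeconomic, school, city, distance, infrastructure and weather variables. No baseline commuting, activity, knowledge, need satisfaction, motivation or barrier score is on it.

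Baseline enters one model in section 6, a separate regression with "the mean difference (post-intervention minus baseline) of outcome variables as dependent variable".

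The data exist. Section 4.1 says "assessments will be performed at baseline (before the 4-week intervention period) and immediately after the intervention period for both intervention and control groups", and the Abstract adds "whereas ACS and the other study variables will be self-reported using questionnaires at baseline and post-intervention". Cycling skills are the exception: the Discussion explains that safety and time limits "will prevent the cycling skills assessment being carried out at baseline and follow-up, respectively", and section 4.2.2 places their measurement inside intervention sessions 2 and 3.

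**The concern.** An indirect effect is the product of two paths. Allocation supports the first, from intervention to mediator. The second, from mediator to outcome, is an observational association among pupils. Pupils who were already motivated and saw few barriers probably commuted actively before the trial and still do afterwards. Without baseline values, that stable association enters the second path. Multiplied by any shift in the mediator, it looks like mediation even if changing the mediator changes nothing.

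Both ingredients are plausible here. The need-satisfaction scale asks pupils about their usual way of getting to school, which is close to the outcome itself. The course is also designed to move knowledge and attitudes.

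Mediation is a stated purpose: the Discussion says that "mediators must be measured to identify the pathways for achieving future behaviour changes". A false pathway would point later programmes at the wrong components. The total-effect estimates are not touched by this point.

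**Working it through.** The plan gives no figure for the mediation analysis, so there is none to reproduce.

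**Inputs from the protocol.** Six schools, three per arm; 360/6 = 60 pupils per school; with the allowed loss of up to 50% (section 2.3.3), 30 per school.

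**Assumptions, not in the protocol.** Baseline mediator–outcome correlation ρ = 0.2, 0.3 or 0.5; baseline to follow-up stability s = 0.6; mediator shift a = 0.3 SD or 0; school ICC 0 to 0.10; continuous outcome; none of the listed covariates. The true effects of mediator and intervention on the outcome are zero.

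**Size of the spurious indirect effect.** Take M1 = s·M0 + a·X + error and Y1 = s·Y0 + error, with independent errors and unit variances within arm.

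- No baseline terms: b = s²ρ = 0.36ρ, so a·b = 0.3 × 0.36ρ = 0.108ρ, which is 0.022, 0.032 and 0.054 SD.
- Change scores for mediator and outcome: covariance (1−s)²ρ = 0.16ρ; variance of mediator change 0.16 + (1−0.36) = 0.80; b = 0.20ρ; a·b = 0.06ρ, which is 0.012, 0.018 and 0.030 SD.
- Both baselines as covariates: b = 0.

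**How often false mediation is declared.** Monte Carlo, 600 runs per setting, 95% interval for the product, pupil-level analysis, a = 0.3 SD. Ranges run over the ICC values.

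| Pupils per school | Baseline handling | ρ = 0.2 | ρ = 0.3 | ρ = 0.5 |
|---|---|---|---|---|
| 60 | none | 18–21% | 32–44% | 61–76% |
| 60 | change scores | 8–13% | 14–18% | 37–40% |
| 60 | both baselines | 4–5% | 3–6% | 3–5% |
| 30 | none | 7–9% | 12–16% | 29–36% |
| 30 | change scores | 4–5% | 5–8% | 12–16% |
| 30 | both baselines | 3–4% | 1–4% | 2–3% |

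Simulated mean indirect effects at 60 per school agree with the formulas: 0.021–0.022, 0.031–0.034 and 0.053–0.054 with no baseline terms, and within 0.001 of zero with both.

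**No mediator shift (a = 0), 60 per school.** The mean indirect effect is zero to within 0.001 whatever ρ is. Without baseline terms the false rate is about 1–4% at ICC 0, 3–14% at ICC 0.05 and 7–23% at ICC 0.10. The rise comes from chance imbalance between three and three schools. With both baselines it is 0.5% or less.

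**Less favourable case.** Suppose correlated stable traits, each measured with error, drive the association (N = 360 independent pupils, a = 0.4 SD, ρ = 0.2 to 0.4, test-retest correlation r). Unadjusted, b = ρ and a·b = 0.08 to 0.16 SD. With both baselines, b = ρ(1−r)/(1+r−2ρ²):

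- r = 0.5: 0.10/1.42 = 0.070 to 0.20/1.18 = 0.169, so a·b = 0.028 to 0.068 SD.
- r = 0.7: 0.06/1.62 = 0.037 to 0.12/1.38 = 0.087, so a·b = 0.015 to 0.035 SD.

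Simulated false rates are 93–96% unadjusted, and 26–89% (r = 0.5) or 11–38% (r = 0.7) adjusted. Adjustment helps but does not cure.

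**The case against.** The strongest reply is that this reads silence as specification. The covariate list is given for the regression models, a phrase last used for the change-score analysis, and a condensed article may leave the equations of an explanatory analysis to a fuller plan. That stands in part: a reader might infer that the mediation models exclude all baseline information, and the text does not establish that. But an enumerated list that reaches weather and date of birth while omitting baseline behaviour is more than missing detail. Change scores, the one baseline form that the plan names, still leave 8–40% at 60 per school.

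A reader might also infer that any baseline correlation will be reported as a pathway. It will not: with no mediator shift the indirect effect averages zero, and a false pathway needs a shift or a chance imbalance between schools.

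Three further objections hold as limits on size:

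- If the list does apply to mediation, home–school distance, bicycle ownership and family background would absorb some of the confounding; the simulation includes none of them.
- Usual cycling is binary and rare. At the 0.3% to under 2% quoted in the Introduction, 360 pupils give 360 × 0.003 ≈ 1 to fewer than 360 × 0.02 ≈ 7 cyclists, so the rates above do not transfer to it.
- Baseline adjustment cannot apply to every mediator. Skills have no baseline, and peer support is defined in section 4.2.2 as a percentage per school, which gives six values.

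**Conclusion.** The point holds in this form: section 6 names no baseline outcome or mediator for the mediation models, most of these values are collected in both arms, and the mediator-to-outcome path is open to pre-existing correlation. Under the stated assumptions, false mediation runs at roughly 18–76% without baseline terms at 60 pupils per school (7–36% at 30), against about 3–6% with both baselines at 60. The correlations, the stability and the mediator shift are assumed, not taken from the protocol. The figures are most relevant to continuous outcomes such as accelerometer activity, and the gain is smaller if stable traits measured with error lie behind the association. This should be changed because it bears on a stated aim, but it does not threaten the main comparison of the arms.

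**What to change.** Add to the mediation paragraph of section 6: *Each mediation model will include, in both the mediator and the outcome equation, the baseline value of the outcome and, where one is collected, the baseline value of the mediator. Cycling skills are not measured at baseline and cannot be handled in this way. Peer support will be adjusted in this way only if analysed at individual level and not as a school percentage. Indirect effects will be interpreted as adjusted associations, because residual confounding of the mediator–outcome path remains.*

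The cost is this short passage and two extra covariates per model, with no new data collection. Pupils with a missing baseline value need a stated handling rule, and reported indirect effects will probably be smaller.
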